### 2.7. Study Procedure

The study will run for 10 weeks (Figure 2), starting with a one-week pre-intervention phase, followed by three weeks of intervention (or control), one week crossover phase, three weeks of control (or intervention), and a two-week post-intervention phase. The 3-week intervention period was selected to balance feasibility assessment with participant burden, consistent with pilot study methodology [39,40]. This duration provides adequate time to evaluate key feasibility outcomes while generating preliminary effect estimates to inform sample-size calculations for a definitive trial. Prior digital health intervention pilots have used a similar intervention period to assess the feasibility of technology-based interventions [41,42,43].

Week 1 (Pre-Intervention): The study team will call the dyad to confirm receipt of the study materials and ensure: (1) the appropriate wearing of the Fitbit smartwatches and data capture, (2) receipt of motivational text messages, and (3) access to the educational videos (Table 2). Data collected during this week will not be used for the study.

Weeks 2–4 (Phase I Intervention/Control): The intervention will start with dyads randomized to the intervention arms. Remote tracking of physical activity data will continue in the control arm.

Week 5 (Crossover/Washout): Participants will switch arms (intervention to control and vice versa). Activity data during this crossover week will not be analyzed (Table 2). Participants in the intervention arm will complete six post-intervention surveys (discussed below), and a few will participate in interviews.

Weeks 6–8 (Phase II Intervention/Control): Participants will continue in their new assignments (opposite of initial condition).

Weeks 9–10 (Post-Intervention): Crossover participants in the intervention arm will undergo post-intervention surveys and interviews. All participants will have access to the educational videos and video-guided physical rehabilitation sessions upon completion of the study (Table 2).

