## Abstract

**Background:** Older adults, including those with Alzheimer’s disease and Alzheimer’s disease-related dementias (AD/ADRD), face barriers in maintaining regular physical activity, which increases their fall risk and reduces their quality of life. The Activity Tracking, Care Partner Co-Participation, Text Reminders, Instructional Education, Video-Guided Physical Rehabilitation, and Exercise trial aims to improve physical activity among older adults. This pilot study aims to assess the feasibility and preliminary efficacy of the ACTIVE intervention. **Methods:** ACTIVE is a multi-method, two-arm randomized, analyst-blinded crossover pilot trial with an embedded qualitative component. We will recruit 50 community-dwelling dyads (older adult–care partner, n = 100), with and without mild AD/ADRD, in a 1:1 ratio. Each dyad will be randomized to the intervention or control arm, stratified by AD/ADRD diagnosis. The intervention arm will receive activity tracking, motivational texts, walking exercises, educational videos, and video-guided physical rehabilitation sessions, while the control arm will receive only activity tracking. The intervention will run in two halves: a three-week intervention/control, a one-week crossover phase, and a three-week control/intervention phase. The quantitative outcome measures will include feasibility measures (recruitment, adoption, adherence, acceptability, fidelity, and retention), and measures of preliminary efficacy (activity metrics, fall risk and fear of falling, functional limitations, and quality of life). Qualitatively, we will assess participants’ experiences, and facilitators and barriers to engagement in physical activity through semi-structured dyadic interviews and thematic analysis. **Conclusions:** This pilot study will generate data on the feasibility and preliminary efficacy of the ACTIVE trial. Findings will inform a full-scale implementation trial.

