### 2.4. Study Materials

While all surveys will be delivered using REDCap, we will use an additional six primary tools to deliver the ACTIVE intervention and obtain study data. These tools include (1.) Fitbit/Fitabase, (2.) myACTIVEsteps.com, (3.) printed educational materials, (4.) instructional education videos, (5.) physical therapy videos, and (6.) the Zoom video conferencing application.

Fitbit Inspire 3 Smartwatch and Fitabase: Participants will receive a pre-configured de-identified Fitbit Inspire 3 smartwatch to passively collect activity data, including daily step counts, activity intensity (daily duration of light, moderate, and intense physical activities), and daily heart rate variability. Fitabase, a secure HIPAA-compliant data management platform, will link each device to a study-specific dashboard and capture all transmitted Fitbit data in real time. Also, motivational text messages will be sent from the Fitabase platform to all study participants.

myACTIVEsteps.com Platform: This secure website houses all asynchronous video-guided physical rehabilitation sessions and instructional educational modules [34]. The website automatically captures engagement metrics, including logins, video access, and watch time (in minutes) for both the video-guided physical rehabilitation sessions and educational modules.

Printed Educational Materials: Care recipients and partners will receive printed copies of the Centers for Disease Control and Prevention’s fall prevention resources—“Stay Independent” [35], and “Family Caregivers: Protect Your Loved Ones from Falling” [36].

Instructional Educational Videos: Care recipients and care partners will access three-minute educational videos during the intervention period. The content of these videos was developed by the study team and is grounded in evidence-based fall prevention strategies from the Centers for Disease Control and Prevention (CDC) STEADI initiative [35,36,37]. Care recipient videos will focus on (1) benefits of moving, (2) safe home exercises, (3) fall prevention, (4) pain management, (5) building routines, and (6) long-term strength and independence. Care partners will receive parallel educational modules emphasizing (1) their role in supervision, (2) setting up safe environments, (3) recognizing risks, (4) encouraging safe activity, (5) reinforcing progress, and (6) transitioning support as independence improves.

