### 2.6. Intervention and Control Groups

Dyad participants randomized to the intervention arm will experience all six components of the ACTIVE intervention—Activity tracking, Care partner co-participation, Text reminders, Instructional education, Video-Guided Physical Rehabilitation, and Exercise. Dyad participants randomized to the control group will receive the Fitbit smartwatch only for physical activity tracking. They will be instructed to wear the smartwatch daily during waking hours. They will not receive motivational text messages, instructional education, or video-guided physical rehabilitation content during the intervention period. Dyad participants in the intervention and control arms may choose to discontinue participation at their own request without penalty. If either member of a dyad chooses to discontinue participation, the entire dyad will be withdrawn from the study. Participants will also be encouraged to continue their regular healthcare and daily routines.

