where *Y_idt_* = outcome, *β*_0_ = fixed intercept, *Trt_i_* = treatment indicator, *Seq_i_* = sequence indicator, *Y_id_*_0_ = baseline value of the outcome, *Demi* = dementia status, *Trt × Dem* = treatment-by-dementia interaction, *Trt × Period =* treatment-by-crossover interaction, γ^⊤^*X_i_* = coefficient of covariates, and *b_d_* and *b_i(d)_* are the random intercept for dyad and individual nested within dyad, respectively. Treatment condition (intervention vs. control) and sequence (intervention-first vs. intervention-second) will be included as fixed effects to estimate the average intervention effect and to account for between-participant differences related to assignment order, respectively. Time will be modeled as a continuous weekly measure to capture trends over the six-week follow-up. Period will be modeled separately as a categorical indicator of pre- versus post-crossover phase to distinguish underlying activity trajectories from changes associated with withdrawal of active intervention components. Given the anticipated persistence of learning effects due to the short one-week washout period, the treatment × period interaction will be used to characterize maintenance or attenuation of intervention effects rather than to assume their absence. All analytical models will follow the intention-to-treat principle, and effect sizes with 95% confidence intervals will be reported to inform power calculations for a future definitive trial.

Qualitative Assessment: Semi-structured interviews will be conducted with dyads after completing the intervention phases. Dyads initially randomized to the intervention arm will be interviewed at crossover, while those starting in the control arm will be interviewed after completing the delayed intervention. Interviews will explore barriers and facilitators to smartwatch use, motivational texts, instructional educational modules, engaging in video-guided physical rehabilitation, walking exercise, and co-participating with a care partner. While we estimate conducting 10 to 20 interviews each for those with and without mild AD/ADRD, the exact number will be guided by the achievement of thematic saturation [68,69].

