**Figure 2 jcm-15-01341-f002:**
[figure not shown]
Timeline and schedule of enrollment, interventions, and assessments. A: Activity Tracking; B: Baseline Survey; C: Crossover Period; P: Post-Intervention Survey; I: Interviews; W: Week; X: Point where event occurs.

**Table 1 jcm-15-01341-t001:** Components of the ACTIVE Intervention.

Activity Tracking, Care Partner Co-Participation, Text Reminders, Instructional Education, Video-Guided Physical Rehabilitation, and Exercise	
Component	What It Includes
Activity Tracking	Fitbit Inspire 3 wearable, continuous step count and activity intensity monitoring, synced weekly
Care Partner Co-Participation	Care partner joining to supervise for safety and engage in home exercise, provide encouragement, and assist with technology
Text Reminders	Automated daily motivational text messages tailored to preceding day’s activity
Instructional Education	Digital education modules (short videos + PDFs): safe exercise, fall prevention
Video-Guided Physical Rehabilitation	Scheduled remote PT via video platform: Week 1: three sessions (gait, balance, strength) Weeks 2–4: weekly check-ins with progression Tailored exercise plans provided electronically
Exercise	Daily walking goal (≥15 min), tracked with wearable; progressive increase based on baseline activity

**Table 2 jcm-15-01341-t002:** Summary of the weekly schedule of the ACTIVE Intervention.

Time Point	Dyad Roles
Weeks 1: Pre-intervention	Control + Intervention Dyad: Mailing of printed educational infographics and smartwatch Troubleshooting to ensure data capture
Weeks 2–4	Control + Intervention Dyad: 1. Weekly dyad telephone check-in by research staff 2. Continuous tracking of activity Intervention Dyad Alone: 3. Two-weekly 3 min educational videos 4. Three-weekly video-guided physical rehabilitation schedule 5. Daily motivational texts
Week 5: Cross-over	Switch roles Interviews and Surveys Troubleshooting to ensure data capture
Weeks 6–8	Control + Intervention Dyad: 1. Weekly dyad telephone check-in by research staff 2. Continuous tracking of activity Control Dyad Alone: 3. Two-weekly 3 min educational videos 4. Three-weekly video-guided physical rehabilitation schedule 5. Daily motivational texts
Week 9–10	Interviews and Surveys

ACTIVE: Activity tracking, Care partner co-participation, Text reminders, Instructional education, Video-Guided Physical Rehabilitation, and Exercise—walking.

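### The control condition is described as activity tracking only, but both arms are mailed printed education in week 1, and the unrestricted week 1 call may also expose control-first dyads to texts and videos just before Phase I

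*Protocol article*

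**What the plan says.** **Comparator.** The Abstract contrasts the full package with a control described thus: "while the control arm will receive only activity tracking". Section 2.6 agrees: "Dyad participants randomized to the control group will receive the Fitbit smartwatch only for physical activity tracking". It adds: "They will not receive motivational text messages, instructional education, or video-guided physical rehabilitation content during the intervention period".

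**Week 1.** Section 2.7 has staff telephone the dyad before Phase I. Besides checking watch wear and data capture, the call is to ensure "2) receipt of motivational text messages, and (3) access to the educational videos". No arm is named. The week 1 row of Table 2 is explicit about both arms: "Control + Intervention Dyad: Mailing of printed educational infographics and smartwatch".

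**Other places.** Section 2.2 has dyads create myACTIVEsteps accounts at the enrolment call. It then sends participants the watch, fall-prevention reading and directions for reaching the online videos, again without regard to arm. Section 2.4 lists the printed material among the tools that deliver ACTIVE, and says that "motivational text messages will be sent from the Fitabase platform to all study participants".

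**Analysis.** Section 2.13 takes the effect size from the pre-crossover phase (weeks 2–4) and reports effect sizes to inform the power calculation of a definitive trial.

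**The concern.** In a crossover where carry-over is expected, the first period is the clean comparison, and this plan rightly relies on it. That comparison is only as clean as the control condition in weeks 2–4. If control-first dyads already hold part of the package, or met part of it days earlier, the trial estimates a different contrast from the one it names. A definitive trial planned on that estimate would inherit the mislabelled comparator. Readers would also be told that controls had tracking only when the plan's own table gives them more.

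**Working it through.** No stated figure is in dispute, so the check sets the passages side by side, element by element, for a control-first dyad.

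| Element | Control definition (Abstract, 2.6) | What else the article says | Status |
|---|---|---|---|
| Printed education | Not part of control | Table 2, week 1: mailed to both arms; 2.2 and 2.4 set no arm limit | Explicit contradiction; the print stays in the home through weeks 2–4 |
| Educational videos | Withheld in the intervention period | 2.7: week 1 call ensures access; 2.2: account and access directions for all | Possible exposure before Phase I, inferred from unrestricted wording |
| Motivational texts | Withheld in the intervention period | 2.7: week 1 call ensures receipt; 2.4: sent to all participants | Possible exposure before Phase I, inferred from unrestricted wording |
| Rehabilitation videos | Withheld in the intervention period | Not named in the week 1 call; same website as the educational videos | No stated exposure |

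**Timing.** Section 2.3 assigns arms after the baseline survey, so week 1 steps could differ by arm. Table 2 separates the arms for weeks 2–4 but not for week 1. Week 2 follows week 1 directly. At crossover, by contrast, Section 2.3 inserts a week to let text prompting fade, and says that this week is not meant to remove retained knowledge.

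**Effect on the contrast.** Let μ be the Phase I mean under tracking alone with no earlier exposure, and Δ the effect of the package. Let a_C and a_I be what the early material adds in control and in intervention dyads.

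- Control mean = μ + a_C
- Intervention mean = μ + Δ + a_I
- Phase I contrast = Δ + (a_I − a_C)

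If a_I = a_C, the shared exposure cancels and the contrast is Δ. If a_I < a_C, the contrast falls below Δ by a_C − a_I. The print is the clearest case. If it counts as part of ACTIVE, as its place in Section 2.4 suggests, its effect is already inside Δ. Then a_I = 0 for the print, and the contrast is Δ − a_C. If it does not count, it is a background condition in both arms and the label of the comparator is what is wrong. The documents give no value for a_C, a_I or Δ, so no size follows.

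**Which outcomes.** Section 2.12 gives the mid-intervention surveys to the intervention arm only. Control-first dyads thus have no pre-crossover survey follow-up that could be diluted. The point bears mainly on the Fitbit measures: steps, metabolic equivalents and heart rate variability.

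**The case against.** The strongest reply is that week 1 is a set-up check. Table 2's week 1 row lists neither texts nor videos, and its weeks 2–4 row reserves both for intervention dyads. Section 2.6 withholds them from control. The statement in Section 2.4 about all participants is true of any crossover, since every dyad has an active phase at some point. Section 2.7 gives everyone the videos at study completion, which suggests that access is restricted before then. A condensed article may also leave arm-specific call scripts to the full protocol.

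Much of this stands. A reader might infer that control-first dyads definitely receive texts and videos; no sentence says so, and that part remains a possibility left open by the wording.

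A reader might also infer a known loss of effect, or an inflated sample size for the next trial. The documents do not support either: exposure shared by both arms cancels if effects add, and no amount of exposure is given. The passage on persistence, "Given the anticipated persistence of learning effects due to the short one-week washout period", concerns three weeks of the full package, so it does not show similar carry-over from a set-up call. Nor is a week 1 activity baseline spoiled, because Section 2.7 excludes that week's data from the study.

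The reply does not dispose of the print. Table 2 sends it to control dyads by name, they keep it during Phase I, and both definitions of control leave it out. Excluding week 1 data does not undo exposure either. And if only a technical check is meant, the call description should say so, since it names motivational messages and not test messages.

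**Conclusion.** The point holds as an inconsistent definition of the comparator. What is certain is that control-first dyads hold printed fall-prevention education during the phase that supplies the effect size, while the article describes them as having tracking only. What is possible, from wording that sets no arm limit, is exposure to motivational texts and educational videos immediately before that phase. Any dilution is of unknown size. It assumes that early exposure adds less in the intervention arm than in control; for the print, that follows if the print counts as part of ACTIVE. The pilot is sized for the precision of its feasibility measures, so its main purpose is not threatened. The preliminary effect estimate and its label are what need correcting.

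**What to change.** Reconcile the Abstract, Sections 2.2, 2.4, 2.6 and 2.7, and Table 2, so that each states by arm who receives texts, video access and print in week 1.

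- In week 1, check only the watch and a neutral test message, in both arms.
- Open motivational texts and the myACTIVEsteps videos to each dyad only when its active phase starts (week 2 or week 6).
- Either mail the printed material at that point, or restate the comparator throughout as activity tracking plus printed fall-prevention material.

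The second option for the print is legitimate and needs only the label. It is also the only one open for dyads that have already been mailed the material.

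The cost is platform access dates, call-script wording and at most a second mailing to control-first dyads.

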Dyads that consent will complete a self-administered baseline survey (discussed below). Also, during the video call, the study team will guide the care recipient and care partner in creating user accounts on myACTIVEsteps.com and Fitabase, and on the Fitbit smartwatch (discussed below), using their preferred names, user identities (IDs), and phone numbers. Each video enrollment session is expected to last between 45 and 60 min. After the video call, the study materials (Fitbit smartwatch, educational materials on fall prevention, and instructions for accessing the online videos and using the smartwatch) will be sent to study participants within 1 week of enrollment. All surveys and consents will be administered remotely on Research Electronic Data Capture (REDCap) [33]. All study participants will be informed that de-identified ACTIVE study data may be used for future ancillary studies without additional participant contact, subject to IRB approval.

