Preliminary efficacy will focus on changes in activity metrics and psychosocial measures. The activity metrics will include daily step counts, daily metabolic equivalent of task, and daily average heart rate variability. These measures are pre-computed metrics on Fitabase. The psychosocial measures will include perceptions, attitudes, and practices related to physical activity, fall risk, fear of falling, functional limitations, and quality of life.

We will assess perceptions, attitudes, and practices regarding physical activity using the Perception of Physical Activity Benefits for Older Adults scale (α = 0.92), the Attitude towards Physical Activity Scale (α = 0.77), and the Physical Activity Practice Scale (α = 0.91) [53]. These perception, attitude, and practice scales each comprise 14, seven, and nine items, respectively. Higher scores on the scales indicate higher perceived benefits, a more positive attitude, and more engagement in physical activities [53].

We will define fall risk using the Stopping Elderly Accidents, Deaths, and Injuries (STEADI)—a 12-item scale (Area Under Curve: 0.91) [37,54]. Higher STEADI scores indicate higher fall risk [37,54]. Fear of falling will be measured using the 16-item Falls Efficacy Scale–International (FES-I; α = 0.96) [55]. Higher FES-I scores indicate greater fear of falling [55]. Functional limitations will be measured using the 6-item Katz Activities of Daily Living (α = 0.85) and the 8-item Instrumental Activities of Daily Living surveys (α = 0.94) [56,57]. Higher scores on these activity surveys indicate greater independence in basic and instrumental activities of daily living [56,57]. Quality of life will be assessed using the Physical and Mental Quality of Life Short Form-12 Health Survey (α = 0.87–0.90) [58]. Higher scores on the Short Form-12 indicate better physical and mental quality of life [58].

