### 2.12. Data Collection by Study Phase

At baseline, dyads will complete sociodemographic and health surveys and background efficacy measures (Figure 2). During the mid-intervention assessment (intervention arm only), care recipients and care partners will repeat all baseline surveys (excluding the sociodemographic and health surveys) and additionally complete the revised Technology Acceptance Model and the System Usability Scale. At the crossover phase, selected dyads who began in the intervention arm will participate in qualitative interviews. At the end-of-study assessment, dyads who completed the delayed intervention will repeat all surveys, and some will be selected for qualitative interviews.

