**Table 3 jcm-15-01341-t003:** Summary of outcome and covariate variables, including sources of data and how each measure is defined.

Outcome Measures	Analysis	Data Source
Recruitment		
1. % of dyad recruited 2. % of dyad randomized	Benchmark: ≥75%	REDCap REDCap
Adoption (measured in week 1)		
1. Smartwatch use ≥ 3 days	Benchmark: ≥75%	Fitabase
2. Motivational Texts ≥ 1 opened		Fitabase
3. Virtual PT videos ≥ 1 sessions		myACTIVEsteps
Adherence (measured weeks 1–3)		
1. Smartwatch use: % days ≥ 8 h	Benchmark: ≥75%	Fitabase
2. Videos: % sessions completed		myACTIVEsteps
3. Virtual PT: % completed		myACTIVEsteps
Acceptability (Week 5 and 9)		
1. Website SUS score 2. Virtual PT SUS Score	Benchmark: Mean ≥ 68	REDCap REDCap
1. Smartwatch TAM Score	Benchmark: Mean ≥ 4.0	REDCap
2. Motivational Texts TAM Score		REDCap
3. Educational Videos TAM Score		REDCap
4. Virtual PT TAM Score		REDCap
Fidelity (Week 5 and 9)		
1. % motivational text sent 2. % educational text notification sent	Benchmark: ≥90%	Fitabase Fitabase
Retention		
1. % of dyad completed the study	Benchmark: ≥75%	REDCap
Preliminary Effectiveness (Week 5 and 9)		
1. Activity: MET-mins/week	Linear Mixed Effect Model	Fitabase
2. FES-I score pre/post		REDCap
3. ADL/IADL score		REDCap
4. SF-12 pre/post		REDCap
5. KAP Scores–pre/post		REDCap
Covariate Measures (Assessed at Baseline)		
Sociodemographic: Age, Sex, Race/Ethnicity, Health Insurance, Education, Marital Status, Living Situation		REDCap
Health Measures: Clinical Frailty Scale, Charlson Comorbidity Index,		REDCap

PT: Physical Therapy; SUS: System Usability Scale; TAM: Technology Acceptance Model; MET: Metabolic Equivalent of Task; FES-I: Fall Efficacy Scale-International; ADL/IADL: Activities of Daily Living/Instrumental Activities of Daily Living; SF: Short Form; REDCap: Research Electronic Data Capture.

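### Week-1 smartwatch data are barred from use, so the baseline covariate in Equations 5 and 6 has no source for steps, METs and heart rate variability

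*Protocol article*

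**What the plan says.** Section 2.7 sets the calendar as "starting with a one-week pre-intervention phase, followed by three weeks of intervention (or control), one week crossover phase". It describes week 1 as a check on watch wear and data capture, receipt of texts and access to videos, and then states: "Data collected during this week will not be used for the study". It also leaves the week-5 activity data out of the analysis.

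Section 2.10 defines the objective outcomes: "The activity metrics will include daily step counts, daily metabolic equivalent of task, and daily average heart rate variability". Their source is the device platform: "These measures are pre-computed metrics on Fitabase". Under Section 2.2 the watch is among the materials that "will be sent to study participants within 1 week of enrollment". Section 2.12 describes baseline collection as surveys.

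Section 2.13 applies the linear mixed models to the three activity metrics and seven behavioral measures. It lists baseline values among the fixed effects, defines Y_id0 as the "baseline value of the outcome", carries it in both Equation 5 and Equation 6, and starts the time index at baseline. The effect size is taken from Equation 5, the pre-crossover comparison.

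**The concern.** The exclusion in Section 2.7 and the model in Section 2.13 cannot both be followed for the activity metrics. This is not a detail left to a separate analysis plan. The article fixes both statements, and a later document would have to override one of them.

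At stake are the only objective efficacy outcomes. Section 2.13 says the effect sizes will inform power calculations for a definitive trial, so their precision matters even in a pilot. Equation 5 compares arms of about 25 dyads, where chance differences in habitual activity can be sizeable and a baseline covariate is most useful. If the conflict stays open, an analyst may have to choose a baseline after data are in hand. The first week of Phase I would be an obvious candidate, but one arm is already receiving the intervention then, so adjusting for it would remove part of the effect being estimated.

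**Working it through.** **1. Trace of possible baseline sources for the three Fitabase metrics**

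| Window | Status in the plan |
|---|---|
| Enrollment call | No watch yet; it is sent afterwards (Section 2.2). Baseline collection is surveys (Section 2.12) |
| Week 1 | Watch worn and data capture checked, but data excluded (Section 2.7) |
| Weeks 2–4 | Phase I, already intervention or control |
| Week 5 | Activity data not analyzed (Section 2.7) |
| Weeks 6–8 | After crossover |

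Usable pre-intervention activity values: none. The multiple imputation planned in Section 2.13 cannot fill the gap, because a covariate missing for everyone leaves no observed values to impute from. The Physical Activity Practice Scale is self-report and is not a baseline for steps, METs or heart rate variability. The seven behavioral measures do have a baseline, from the enrollment surveys.

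**2. The plan's own precision figure (Section 2.8)**

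The point does not depend on this figure, but the illustration below borrows its design effect.
- SE = √(0.75 × 0.25 / 100) = 0.0433
- Design effect = 1 + (2 − 1) × 0.2 = 1.2
- Adjusted SE = 0.0433 × √1.2 = 0.0474
- 95% CI = 0.75 ± 1.96 × 0.0474 = 0.657 to 0.843

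These match the stated 0.043, 0.047 and 0.66–0.84.

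**3. Illustration of the precision at stake in Equation 5**

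Inputs: about 25 dyads, hence 50 persons, per arm; design effect 1.2; outcome in SD units; one measurement per person; no other covariates. The baseline/follow-up correlation r is assumed, because the document gives none.

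- Without baseline: SE = √(1.2 × (1/50 + 1/50)) = √0.048 = 0.219; half-width = 1.96 × 0.219 = 0.43 SD
- With baseline: half-width = 0.429 × √(1 − r²)

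| r (assumed) | 1 − r² | 95% half-width (SD) | Variance ratio, without / with baseline |
|---|---|---|---|
| 0.5 | 0.75 | 0.37 | 1.33 |
| 0.7 | 0.51 | 0.31 | 1.96 |
| 0.8 | 0.36 | 0.26 | 2.78 |

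**The case against.** The strongest reply concerns consequence. Only three of ten outcomes are affected. Section 2.8 says the trial is not powered for efficacy, and the feasibility benchmarks and go/no-go decision do not use Y_id0. Without the term, the randomized contrast in Equation 5 remains unbiased. Equation 6 uses both periods, so it holds within-person information without a baseline covariate. All of this stands. It limits the damage to precision in one family of outcomes, but it does not remove the contradiction, and the plan takes its effect size from Equation 5.

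The illustration is also open to challenge. It compares baseline adjustment with no adjustment at all, whereas Equation 5 already has demographic, frailty, comorbidity and dementia terms and repeated values. Some of the gain would already be absorbed. The intra-cluster correlation of 0.2 was assumed for a feasibility proportion, not for steps. These points stand too, so the figures show scale only.

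Using week 1 is not a complete remedy by itself. Allocation follows the enrollment survey (Section 2.3), so week 1 probably comes after randomization. Receipt of texts and access to videos are checked that week. Table 2 lists mailing of the watch under week 1, so wear days may be few. Adjusting for a week-1 value that already differs by arm because of intervention content could bias the contrast. This objection is sound and shapes the fix.

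A reader might also infer that the exclusion clashes with Table 3, which dates adoption to week 1 and adherence to weeks 1–3, and that the adherence window cuts off the last intervention week of Phase I. The document does not support that. Section 2.10 defines adherence over the three-week intervention period, and Table 1 also numbers by intervention week. In study weeks 1–3, control-first dyads would have no sessions to complete, so that reading is not credible.

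Figure 2 is not shown and may mark tracking in week 1, but such a mark would not cancel the exclusion in Section 2.7.

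**Conclusion.** The contradiction holds for steps, METs and heart rate variability. As written, Equations 5 and 6 cannot be fitted to these metrics because Y_id0 has no permitted source. It does not hold for the survey outcomes.

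A reader might go further and conclude that the efficacy analysis as a whole fails or that the treatment effect would be biased. Neither follows. Leaving out the baseline term costs precision only.

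Under the stated simplifications and assumed r of 0.5 to 0.8, the cost is a half-width of about 0.43 SD instead of 0.37 to 0.26 SD. The real difference is likely smaller. The existence of the conflict rests on the text alone; only its size rests on assumptions. It should be settled before any activity data are analyzed.

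**What to change.** Amend the sentence in Section 2.7 so that week-1 Fitbit data are used only as Y_id0 for the three activity metrics. Specify:

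- **Valid days:** at least 8 h of wear, which is the plan's own wear rule, excluding the set-up day.
- **Clean window:** no motivational texts, videos or other intervention content to either arm during it. Any delivery test should be identical in both arms and fall outside the window.
- **Allocation:** preferably disclosed to dyads after the window closes.
- **Too few valid days:** a stated rule, for example imputation of the baseline covariate.

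If such a window cannot be secured, remove Y_id0 and the baseline time point for these three metrics and acknowledge the lost precision.

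The cost is small, since the watch is already worn and its data captured in week 1. It is more than a wording change, however, because the clean window and the timing of disclosure are operational rules. The remaining drawbacks are that week 1 includes set-up and novelty effects, may yield few valid days, and follows randomization.
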